### Investigation of haematuria

Participants in Cohort 1 and those randomised to the haematuria arm of Cohort 2 will be investigated for the presence of haematuria (figures 1 and 2). If a single positive result is identified on research nurse review of the erythrocyte test parameter, then the participant will be invited to attend an Early Detection Clinic (run in a nearby GP surgery and staffed by study-employed or NIHR Clinical Research Network (CRN)-employed nursing staff) within 4–6 weeks of assessment of their results. At this clinic, participants will undergo a urinary tract ultrasound scan (USS) and provide a urine sample for cytology. Those with an abnormal USS (bladder or renal mass suggestive of cancer detected) or abnormal cytology will be referred by their GP or the research nurse team (following standard NHS 2ww criteria) to their local urology haematuria service for evaluation (flexible cystoscopy and additional assessments). We expect that around 20% of participants with self-testing haematuria will require referral. The test results for these participants will be obtained directly through the relevant urology departments and categorised into: BCa diagnosis, kidney cancer diagnosis, upper tract urothelial cancer diagnosis, urinary stones, infection or inflammation, stricture, clinically benign prostatic enlargement, post-TURP (transurethral resection of the prostate), diagnosis unclear/further tests planned, likely prostate cancer, no abnormal finding or other finding. Participants with normal USS and normal cytology, from the early detection clinic, will receive a letter explaining this and discharging them from the study. They will receive advice about the need to see their GP if they have urinary symptoms or VH. Their GP will receive a letter with advice about management of NVH. Participants without haematuria will receive a letter confirming their result and informed that their GP will also be notified of their results. They will be asked to seek a GP appointment if they develop urinary symptoms in the future. Participants in cohort 3 will undergo standard NHS assessment of haematuria as part of their referral process (regardless of their test strip results). This includes cystoscopy and upper tract imaging (typically CT urogram and USS).

### Investigation of glycosuria

Participants randomised to the glycosuria arm of Cohort 2 will be investigated for the presence of glycosuria. Glycosuria was chosen as it is a validated urine test that can detect a meaningful disease (diabetes mellitus), whose outcomes are better detected at an early stage. If a single positive result is identified on research nurse review of the glucose test parameter, then the participant will be invited to attend an Early Detection Clinic within 4–6 weeks of assessment of their results. At the clinic, participants will undergo hemoglobin A1c (HbA1c) blood testing. Those with elevated HbA1c (as defined by local reference ranges) will be referred to their GP for diabetic management. Those with a normal HbA1c (as defined by local reference ranges) will receive a letter explaining that their test was normal and will be advised to see their GP if they think they have diabetic symptoms. Their GP will also be informed of the test result. Participants in the glucosuria testing arm without glycosuria will receive a letter confirming their normal result and informed that their GP will also be notified of their results. Participants will be advised to seek a GP appointment if they develop diabetic symptoms.

### Consent

On receipt of the postal urine self-testing kit, participants will be able to choose an action to take:

Consent to enter trial: those wishing to take part in the trial will be asked to consent to participate by agreeing to consent statements in the mobile App or freephone system, before proceeding to complete the study questionnaire, and then self-testing with the test strips. Invitees will be prompted prior to providing results to have read the Participant Information Sheet.Non-response: non-responders (ie, do not consent or provide test results via the mobile App or freephone)

Following a positive urine self-test result for haematuria (Cohort 1) and haematuria/glucosuria (Cohort 2) participants will receive a telephone call from a study research nurse to explain their results and schedule an Early Detection Clinic appointment.

This will be followed by the mailout of a second Patient information sheet (PIS) detailing what will happen at the Early Detection Clinic appointment. At the clinic, written informed consent will be obtained prior to any trial-specific procedures (online supplemental material). The chief investigator (CI) will ensure that those with delegated responsibility to obtain informed consent are duly authorised, trained and competent according to the ethically approved protocol, principles of Good Clinical Practice (GCP) and Declaration of Helsinki. The right of a participant to refuse participation without giving reasons will be respected.

10.1136/bmjopen-2023-076612.supp1Supplementary data

Cohort 3 participants will receive a self-testing kit including a study invitation letter and PIS detailing what will happen at the 2ww appointment (figure 3). The invitation letter will be from the routine care team at the participating urology department. On presentation to the 2ww appointment, written informed consent will be obtained prior to any trial-specific procedures. Translation via hospital interpreters is acceptable if required. The principal investigator will ensure that those with delegated responsibility to obtain informed consent are duly authorised, trained and competent according to the ethically approved protocol, principles of GCP and Declaration of Helsinki. The right of a participant to refuse participation without giving reasons will be respected. For Cohort 3, participation is mostly altruistic as the participants will already be in the NHS pathway and will have the gold-standard tests for detection of BCa.

### Sample size(s)

A formal power calculation is not appropriate for this trial due to its feasibility-related outcomes. The current planned sample size is to invite 2000 participants in Cohort 1, (estimated 800 enrolled), invite 3000 male participants in Cohort 2, (estimated to enrol and randomise 1200) and invite 1000 participants in Cohort 3 (estimated enrolment of 500).

### Randomisation

Cohort 2 will be randomised between two arms where either the haematuria or glycosuria result will be revealed during the trial. Participants will be randomised via permuted blocks to ensure approximately equal numbers in the two arms. The randomisation lists will be generated by the trial statistician. The central nursing team will randomise participants prior to review of self-test results. Participants will not be given any details of the allocated group until they receive their initial results letter.

### Primary outcomes

This is a feasibility study and so there are multiple primary outcomes reflecting each stage of the study and what we need to understand for a larger phase III randomised controlled trial:

1. Acceptability of urine self-testing and the Early Detection Clinics will be measured by:

1.1. Proportion of invitees who report results for at least one test strip.

1.2. Proportion of participants who attend and consent for cytology and urinary tract ultrasound following detection of haematuria on self-testing.

1.3. Proportion of participants who attend and consent for HbA1c blood testing following the detection of glycosuria on self-testing.

2. Compliance with urine self-testing will be measured by;

2.1. The proportion of participants who report results for (i) all six test strips and (ii) three or more test strips.

2.2. The number of test strips returned on average in those who return at least one test strip.

3. Prevalence of haematuria will be measured from the proportions of participants with ≥1 test strip positive for haematuria.

4. Prevalence of glycosuria will be measured from the proportions of participants with ≥1 test strip positive for glycosuria.

5. Haematuria clinic outcomes will be measured via:

5.1. The proportion of participants with a positive or abnormal cytology in those where a urine sample is collected.

5.2. The proportion of participants who have an abnormal USS, who underwent scanning.

6. Glycosuria clinic outcomes will be measured via the proportions of those with an elevated HbA1c following collection of a blood sample.

7. Urinary symptoms will be measured via symptom scores from the urine symptoms questionnaire (as completed prior to self-testing).

8. BCa in the tested population will be measured via the proportions of BCa cases and corresponding stage in identified participants (excluding non-responders and withdrawals).

9. The accuracy of self-testing, cytology and USS will be measured via:

9.1. The sensitivity, specificity, PPV and negative predictive value (NPV) of the following in men and women with cancer as identified by cystoscopy results at the 2ww appointment

9.1.1. Self-testing (App vs freephone).

9.1.2. Cytology and ultrasound (separately and in combination) as a triage test in those with positive haematuria

9.2. The predictive value of symptoms in combination with self-testing:

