#### Study aims and objectives

Three cohorts will be studied in this feasibility study. Each will address a separate aim, all of which are needed to develop a phase III prospective trial:

Aim 1: Cohort 1 will test compliance, prevalence of haematuria and BCa and the economics of the trial within a screening-engaged population. It might suggest that BCa screening works best when embedded within lung screening services. It will also test women and populations younger than typical for the highest risk BCa age group.Aim 2: Cohort 2 will test compliance, prevalence of haematuria and BCa, prevalence of glycosuria and undiagnosed diabetes within a high-risk community-based population.Aim 3: Cohort 3 will provide a positive predictive value (PPV) of the study tests (urine self-testing, urine cytology and ultrasound) as assessed in a population already referred in the NHS 2ww haematuria pathway.

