**Figure 1 F1:**
[figure not shown]
Recruitment and flow within Cohort 1 within the YORKSURe study: male and female participants will be solely recruited from the YLST. USS, ultrasound scan; YLST, Yorkshire Lung Screening Trial.

Eligibility for Cohort 2: Men aged 65–79 identified through a database search at 8–10 selected GP practices considered to be in high-risk BCa mortality areas in South Yorkshire (figure 2).

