### Exclusion criteria

#### Cohort 1

Unable to or did not consent to contact from other research teams.Insufficient capacity to give consent to take part in the research as determined by the investigator taking consent.

#### Cohort 2

Participant has opted out of their NHS data being used for research via the National Data Opt-Out.Prior diagnosis of bladder or kidney cancer.Diagnosis with any other cancer within the past 5 years (except non-melanoma skin cancer).Insufficient capacity to give consent to take part in the research, defined as the presence of the following conditions coded in the GP records: dementia, Alzheimer’s disease or Parkinson’s disease; or as determined by the investigator taking consent.

#### Cohort 3

Unable to provide written informed consent.Insufficient capacity to give consent to take part in the research, defined as the presence of the following conditions coded in the GP records: dementia, Alzheimer’s disease, or Parkinson’s disease; or as determined by the investigator taking consent.Evidence in patient medical record of historic dissent to use of data in research or participant has opted out of data use via the National Data Opt-Out.

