### Screening tests and self-testing

Participants in all three cohorts will be provided with home urine self-testing kits produced and supplied by Testcard. The kit contains 6× Roche Combur 5 HC test strips for the graduated determination of glucose, leucocytes, nitrites, protein and erythrocytes. Blood and glucose will be tested for primary study purposes. The other three parameters (leukocytes, nitrite, protein) will be analysed as part of an exploratory objective.

Participants will record six continuous days of test strip results via a bespoke study App or study freephone service. Prior to commencing self-testing, participants will complete a bladder symptom questionnaire (a modified and unvalidated version of the Urinary Tract Infection Symptom Assessment (UTISA) Questionnaire).^25^ The questionnaire will collect demographic data and information on bladder symptoms within the past 4 weeks including presence of VH. The questionnaire will be pseudonymised and all data pertaining to the questionnaire will be kept separate from urine self-testing results until the end of the trial. The app will capture a digital photograph of the test strip, which will be interpreted by a research nurse against the Roche Combur 5 HC colour chart. Test strip results will not be available to participants at the point of self-testing.

It is anticipated and expected that some participants in the study population will either not have a smartphone, or will not be confident in using a mobile App. A study freephone service will therefore be available as an alternative option for recording self-test results. The freephone service will be an automated system whereby participants use their keypad to enter their responses to the questionnaire and test strip results. The freephone service requires confirmation of the test strip colour result by the participant against the Roche Combur 5 HC colour chart, whereas App users will simply take a photograph of their completed test strip which will be submitted for interpretation by a research nurse.

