### Data collection

Self-test results and questionnaire data will be captured in the bespoke mobile app and freephone system. The questionnaire will collect information on diabetes (diagnosis and management), smoking status, ethnic group, lesbian, gay, bisexual, and transgender (LGBT) identification, highest level of education, history of factory work as well as bladder symptoms (via a modified and unvalidated version of the UTISA Questionnaire^25^). Cohort 1 and 2 data collected at Early Detection Clinics will be entered into a REDCap^26^ database and will include height and weight, current occupation, previous longest occupation, concomitant medication, ultrasound results, urine cytology results and HbA1c results. Data for Cohort 1 and 2 participants who are subsequently referred for a 2ww, and consenting Cohort 3 participants, will be obtained via medical records to include results of cystoscopy, ultrasound/CT, cytology and cancer staging where applicable. At 14–30 days post cystoscopy, these participants will be contacted to collect information of any treated incidences of UTI following cystoscopy. Passive follow-up data (identification of cancer diagnosis and stage) will be collected through the NCRAS at 1, 2 and 3 years after the end of the trial for all participants who have self-tested (excluding withdrawals). Summary data will also be collected through NCRAS, requested by geographic area, for a population comparable to Cohort 2.

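### Aim 2 includes undiagnosed diabetes in Cohort 2, but no listed outcome estimates it: outcome 6 pools men with known diabetes and new cases

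*Protocol article*

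**What the plan says.** All references are to the protocol article.

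- **Study aims and objectives, Aim 2.** Among other things, Cohort 2 is to test "prevalence of glycosuria and undiagnosed diabetes within a high-risk community-based population".
- **Study design and setting.** Cohort 2 is "Men aged 65–79 identified through a database search at 8–10 selected GP practices". Diabetes status is not a condition of entry.
- **Exclusion criteria, Cohort 2.** The list includes "Prior diagnosis of bladder or kidney cancer", along with data opt-out, other recent cancer and lack of capacity. Known diabetes is not on it.
- **Investigation of glycosuria.** The test was chosen because "it is a validated urine test that can detect a meaningful disease (diabetes mellitus), whose outcomes are better detected at an early stage". On who goes to the clinic: "If a single positive result is identified on research nurse review of the glucose test parameter, then the participant will be invited to attend". There is no exception for men already diagnosed.
- **Primary outcomes.** Outcome 1.3 is attendance and consent for HbA1c, outcome 4 is the share of participants with at least one glucose-positive strip, and outcome 6 reads "Glycosuria clinic outcomes will be measured via the proportions of those with an elevated HbA1c following collection of a blood sample". None refers to prior diabetes.
- **Statistical analysis.** Percentages with 95% Wilson intervals are given per cohort, including the HbA1c result among those referred. No split by diabetes status is stated.
- **Data collection.** The questionnaire asks about diagnosis and management of diabetes, and the clinic records concomitant medication.
- **Screening tests and self-testing.** "all data pertaining to the questionnaire will be kept separate from urine self-testing results until the end of the trial".

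**The concern.** The aim concerns diabetes that nobody has yet found. The outcome that would answer it counts any elevated HbA1c in a man who gave blood, including men whose diabetes is already on record. Such men can reasonably be expected to show glycosuria and an elevated HbA1c more often than others. They can therefore enter both the numerator and the denominator of outcome 6.

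The treatment of the two targets in Cohort 2 is uneven. Men with a previous bladder or kidney cancer are removed, so the haematuria arm looks for new disease. Men with previous diabetes stay in, and no outcome sets them apart. Yet the stated reason for choosing glycosuria is early detection, which concerns new cases.

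At stake is one named aim of the feasibility study. If the outcomes are followed as written, the main trial would be planned without an estimate of how much new diabetes the reciprocal test finds, and the pooled figure could be taken for it. The same figure could also enter the exploratory health economics item that counts cancers and other illnesses in each arm.

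**Working it through.** **1. Matching the aim to the outcomes.** The diabetes part of Aim 2 has two components.

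- Prevalence of glycosuria: outcome 4 answers this directly.
- Prevalence of undiagnosed diabetes: outcome 6 is the only listed outcome using HbA1c results. Its denominator is everyone who gave blood and its numerator is everyone with an elevated value. No other primary, secondary or exploratory outcome is defined on men without known diabetes. This component has no outcome.

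**2. Size of the arm.** The Sample size section estimates that 1200 men will be enrolled and randomised from 3000 invited (1200/3000 = 40%). With approximately equal arms, 1200/2 = 600 men are in the glycosuria arm.

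**3. Illustration of the mixing.** The document gives no prevalence of known or undiagnosed diabetes and no strip-positivity rate. Every rate in this step and the next is an assumption.

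For n = 600, let k be the proportion with known diabetes, u the proportion with undiagnosed diabetes, and s_k and s_u the strip-positive proportions in those groups. Take 1% strip-positive in men without diabetes, 80% of strip-positive known cases with elevated HbA1c, all strip-positive undiagnosed cases with elevated HbA1c, and full clinic attendance. Then:

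- known positives = n × k × s_k
- undiagnosed positives = n × u × s_u
- other positives = n × (1 − k − u) × 0.01
- known cases with elevated HbA1c = 0.8 × known positives

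Middle case, k = 15%, u = 3%, s_k = s_u = 40%:

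- known positives 600 × 0.15 × 0.40 = 36; undiagnosed 600 × 0.03 × 0.40 = 7.2; other 600 × 0.82 × 0.01 = 4.9; total 48.1
- elevated HbA1c: 0.8 × 36 = 28.8 known, plus 7.2 new = 36.0, so 28.8/36.0 = 80% known
- outcome 6 as written: 36.0/48.1 = 75%; in men without known diabetes: 7.2/(7.2 + 4.9) = 59%
- elevated HbA1c as a share of the arm: 36.0/600 = 6.0% pooled; 7.2/600 = 1.2% new (Wilson 95% CI about 0.6% to 2.4%)
- new cases over self-testers without known diabetes: 7.2/(600 × 0.85) = 7.2/510 = 1.4% (Wilson 95% CI about 0.7% to 2.9%)

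Two other cases under the same formulas:

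| k, u, s_k, s_u | Elevated, known | Elevated, new | Known share | Outcome 6, pooled | Outcome 6, no known diabetes |
|---|---|---|---|---|---|
| 5%, 5%, 20%, 40% | 4.8 | 12.0 | 29% | 72% | 69% |
| 20%, 2%, 50%, 30% | 48.0 | 3.6 | 93% | 76% | 43% |

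The pooled outcome 6 barely moves across the three cases (72%, 75%, 76%), while the expected number of new cases falls from 12.0 to 7.2 to 3.6. The pooled figure does not track the quantity in the aim.

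**4. Wider range.** A grid of 720 combinations used k from 5% to 25%, u from 1% to 5%, strip positivity from 20% to 60% in each group, clinic attendance of known cases at 0.5 or 1 relative to the rest, and 60% or 90% of known cases with elevated HbA1c. The known share of elevated results ran from 9% to 99%, with median 75%. It exceeded one half in 80% of combinations, which is a count over the grid and not a probability.

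- Lowest: known 600 × 0.05 × 0.2 × 0.5 × 0.6 = 1.8 against new 600 × 0.05 × 0.6 = 18; 1.8/19.8 = 9%.
- Highest: known 600 × 0.25 × 0.6 × 0.9 = 81 against new 600 × 0.01 × 0.2 = 1.2; 81/82.2 = 99%.

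**The case against.** The best defence is that the data which separate known from new diabetes are collected by design. The questionnaire asks about diagnosis and management before any strip is used, and the clinic records medication. Keeping the questionnaire apart from strip results lasts only until the end of the trial, so it does not block the analysis. A condensed article may leave reporting by a baseline item to the full protocol or analysis plan. Outcome 6 is labelled as a clinic outcome, and as a description of what the clinic finds it is correctly worded.

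Most of this stands, but it does not close the gap. The article names an aim and then defines the relevant outcome, with its denominator, for a different quantity. That goes beyond detail left for later.

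A reader might also infer stronger things that the document does not support:

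- *That the HbA1c results will mostly be known diabetes.* This is plausible, but it rests on rates that the document does not give. It fails when known diabetes is not much commoner than undiagnosed diabetes, or when known cases attend less.
- *That outcome 4 is wrong.* It is not; overall glycosuria prevalence is part of Aim 2.
- *That clinic load is overstated.* Known cases are invited and, if they attend, are real load.
- *That cost per case would be overstated.* Counting known cases as found would lower the apparent cost per new case. The Economic evaluation section describes a model of haematuria screening and mentions no cost per diabetes case.
- *That the bladder cancer results are affected.* The haematuria, compliance and recruitment outcomes are not touched.

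**Conclusion.** The point holds in a limited form. No listed outcome estimates the undiagnosed-diabetes part of Aim 2, because outcome 6 and its restatement under Statistical analysis combine known and new disease. This follows from the text alone and needs no assumption about rates.

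The size of the distortion cannot be fixed from the document. Known cases may form a large share of elevated results, possibly the majority: 9% to 99% over the assumed grid. In the middle illustration the pooled share of the arm is five times the share of new cases (6.0% against 1.2%). These figures show what could happen and are not forecasts.

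Separating known cases would still not give the prevalence of undiagnosed diabetes. Strip-negative men have no HbA1c test, so undiagnosed diabetes without glycosuria is never seen. What can be estimated is the yield of new diabetes detected through glycosuria.

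**What to change.** 1. Add an outcome for Aim 2. The numerator is glycosuria-arm self-testers with no prior diabetes diagnosis who have an elevated HbA1c; the denominator is all self-testers in that arm with no prior diabetes diagnosis. Label it the detection yield of new diabetes through glycosuria, and say that it is not a full prevalence.
2. Report outcomes 1.3, 4 and 6 separately for men with and without known diabetes, keeping the overall outcome 4.
3. Take known diabetes from the questionnaire item, linked to the strip results at the end of the trial. For clinic attenders, use recorded concomitant medication as a second source.
4. If diabetes enters the exploratory count of other illnesses in each arm, count new cases only.

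The cost is wording in the outcome definitions and the analysis plan, settled before analysis. Eligibility, the clinical pathway and data collection do not change. The stated diabetes yield will be smaller, and the intervals for the split outcomes wider. In the middle illustration, outcome 6 among men without known diabetes would rest on about 12 men instead of about 48.
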